## Abstract

**Introduction:**

Patients discharged from Critical Care suffer from excessive longer term morbidity and mortality. Physical and mental health measures of quality of life show a marked and immediate fall after admission to Critical Care with some recovery over time. However, physical function is still significantly reduced at 6 months. The National Institute for Health and Care Excellence clinical guideline on rehabilitation after critical illness, identified the need for high-quality randomised controlled trials to determine the most effective rehabilitation strategy for critically ill patients at risk of critical illness-associated physical morbidity. In response to this, we will conduct a randomised controlled trial, comparing physiotherapy aimed at early and intensive patient mobilisation with routine care. We hypothesise that this intervention will improve physical outcomes and the mental health and functional well-being of survivors of critical illness.

**Methods and analysis:**

308 adult patients who have received more than 48 h of non-invasive or invasive ventilation in Critical Care will be recruited to a patient-randomised, parallel group, controlled trial, comparing two intensities of physiotherapy. Participants will be randomised to receive either standard or intensive physiotherapy for the duration of their Critical Care admission. Outcomes will be recorded on Critical Care discharge, at 3 and 6 months following initial recruitment to the study. The primary outcome measure is physical health at 6 months, as measured by the SF-36 Physical Component Summary. Secondary outcomes include assessment of mental health, activities of daily living, delirium and ventilator-free days. We will also include a health economic analysis.

**Ethics and dissemination:**

The trial has ethical approval from Newcastle and North Tyneside 2 Research Ethics Committee (11/NE/0206). There is a Trial Oversight Committee including an independent chair. The results of the study will be submitted for publication in peer-reviewed journals and presented at national and international scientific meetings.

**Trial registration number:**

ISRCTN20436833.

Strengths and limitations of this studyThe strengths of the study include the relatively large sample size and pretrial power calculation, the inclusion of a range of general Critical Care patients, the multicentre recruitment (although limited to three centres in the north of England), applicability to UK practice, delivery of rehabilitation to the control group; which reflects current UK practice, and prolonged (6 months) follow-up.Limitations include the number of sites and the lack of 7-day rehabilitation interventions. Also, the study is blinded to patient participants, but is not blinded to their healthcare providers.

## Introduction

### Background and rationale

Over 100 000 patients are admitted to Critical Care Units in the UK every year. It has been recognised for some time that patients discharged from Critical Care suffer from excessive longer term morbidity and mortality.^1^ Quality of life (QoL), in terms of both physical and mental health, is significantly reduced following a prolonged admission to Critical Care. In survivors, there is a slow and incomplete recovery in QoL over the next 6–12 months.^2^

In 2009, the National Institute for Health and Care Excellence (NICE) published guidance for rehabilitation after critical illness.^3^ The guideline noted that there were no published randomised controlled trials examining how effective early mobilisation therapy is at reducing the risk of adult patients developing physical and non-physical morbidity after hospital discharge. The authors recommended more research to determine which therapeutic strategies are the most clinical and cost effective at reducing the prevalence and severity of critical illness-associated physical morbidity, psychological morbidity, and cognitive dysfunction.

Since 2009, there have been a small number of published randomised controlled trials of mobilisation therapy in Critical Care. In a study based in two Medical Critical Care Units in North America, 104 patients who were previously functionally independent were randomised to receive either early mobilisation therapy or standard care. Early mobilisation therapy was found to be safe and well tolerated, and resulted in better functional outcomes at hospital discharge, a shorter duration of delirium, and more ventilator-free days compared with standard care.^4^ A single-centre study in medical and surgical Critical Care patients randomised patients to receive either daily standard physiotherapy or daily standard physiotherapy with an active training session using a bedside cycle ergometer. They found that additional exercise training enhanced recovery of functional exercise capacity, self-perceived functional status, and muscle force at hospital discharge.^5^ A single-centre randomised controlled trial in Australia compared normal physiotherapy (active exercises and progressive mobilisation, 6 days/week, until hospital discharge) to an intensive physiotherapy programme started in Critical Care and continued through the ward stay and after hospital discharge.^6^ There were no significant differences in any of the outcome measures at any stage of follow-up although the rate of change over time from first assessment was greater in the intervention group. Recent systematic reviews and meta-analyses identified the need for further controlled trials of better quality and larger sample size studies, including evaluation of type, duration, frequency and intensity of physical therapy.^7–10^

There is, therefore, some evidence that early physiotherapy in this group of severely ill patients may improve both the rate and magnitude of recovery from critical illness. However, the evidence base is incomplete and, in particular, the optimum intensity of physiotherapy is not known. To address this, we will carry out a randomised controlled trial of intensive versus routine physiotherapy in the critically ill.

### Objective

The objective of the study is to compare two different intensities of early physiotherapy on the rate and magnitude of recovery from critical illness in a general Critical Care population of adult patients.

### Study design

We will conduct a multicentre patient randomised, parallel group, controlled trial comparing two intensities of physiotherapy on physical QoL. Adult, critically ill patients, ventilated for more than 48 h, will be randomised to the control or intervention group (figure 1). The control group will receive usual physiotherapy, including a once-daily functional retraining session (Monday to Friday). The intervention group will receive a more intensive physiotherapy programme, including at least one functional retraining session per day (Monday to Friday) and an individualised structured exercise programme.

**Figure 1 BMJOPEN2015008035F1:**
[figure not shown]
Study design.

## Methods

### Eligibility criteria

Participants will be recruited from the Critical Care (Intensive Care or High Dependency) Units of participating hospitals. Eligible patients will be medical or surgical patients aged 18 years or older having received 48 h or more of invasive or non-invasive mechanical ventilation. The exclusion criteria are as follows: patients receiving end-of-life care; patients with acute brain or spinal cord injury; patients admitted following brain or spinal cord surgery; patients with multiple trauma if mobilisation therapy is unlikely to be possible; patients with burns; patients with rapidly progressive neuromuscular disease; patients enrolled in another clinical trial without a co-enrolment agreement in place; patients previously enrolled in the Extra Physiotherapy in Critical Care study. Patients who have suffered cardiac arrest may be recruited if the clinical team believes that there is a possibility of recovery.

### Study intervention

Following randomisation into the trial, each participant will undergo a daily morning sedation hold, with the exception of those participants who have neuromuscular blocking agents administered, where severe agitation is already present despite sedation, or where participants’ ventilatory parameters are so high that a sedation hold would be deemed detrimental to participant safety. The sedation hold will consist of the interruption of all continuous intravenous sedation^11^ and assessment of the patient using the Richmond Agitation-Sedation Scale (RASS).^12^ Participants will be assessed continuously during this period, and sedation re-started (if required) to achieve a sedation level of ‘easily roused and cooperative’ (RASS of −1, 0 or +1). If the sedation hold is successful, the participant will be screened for safety prior to the start of physiotherapy (figure 2). If the participant fails the sedation hold, or a sedation hold is not appropriate, passive range of motion exercises will be performed in all four limbs and the trunk, as deemed appropriate. The assessment of sedation will be repeated for both groups in the afternoon with a second adjustment of sedation if needed. This will control for sedation breaks in that both groups will, on average, have had their sedation controlled in the same manner. Following this, the participants will be screened for safety and undertake physiotherapy as appropriate for the group to which they have been randomised.

**Figure 2 BMJOPEN2015008035F2:**
[figure not shown]
Trial intervention protocol.

The safety screen will be conducted by the treating physiotherapist in conjunction with nursing and medical staff, as necessary. Participants meeting any of the following criteria will fail the safety screen: mean arterial pressure (MAP) <65 mm Hg; heart rate <40 or >130 bpm; respiratory rate <5 or >40 breaths/min; marked ventilator asynchrony; oxygen saturation <88% or, if known respiratory disease, a 10% decrease from normal oxygen saturation; active gastrointestinal bleeding; acute myocardial ischaemia; actively undergoing a procedure; agitation requiring increased sedatives in the last 30 min; insecure airway; other significant events deemed inappropriate by the Critical Care team for the start of active physiotherapy (specifics to be recorded).

Following a successful safety screen, an assessment for wakefulness will be completed. The participant must be able to obey at least three of the following commands:^11^ (1) opening eyes in response to voice; (2)using eyes to follow investigator on request; (3)squeezing hand on request and (4)protruding tongue on request. If the participant can follow at least three of these commands and has a RASS of −1, 0 or +1, they will be deemed as having achieved ‘wakefulness’, and active physiotherapy can start (figure 2).

The physiotherapy techniques used in this trial include functional retraining (figure 3) and individually tailored exercise programmes, based on a muscle-strengthening algorithm (figure 4). During functional retraining, participants will undergo physiotherapy at one of five levels of activity, only moving onto the next level when they are able to achieve the activity at the current level. During the individually tailored exercise programmes, participants will progress from active-assisted exercises through to resisted exercises, via the use of various therapy adjuncts, that is, hand weights, exercise band, and computer game-based exercise. The duration and content of therapy sessions from both treatment groups will be recorded daily.

**Figure 3 BMJOPEN2015008035F3:**
[figure not shown]
Functional retraining flow chart.

**Figure 4 BMJOPEN2015008035F4:**
[figure not shown]
Strengthening programme algorithm.

The control group will receive the standard intensity of physiotherapy which is normally given on participating units. This will consist of no more than 30 min of active exercise comprising: functional retraining (figure 3) and, if time permits, an individually tailored exercise programme, based on a muscle-strengthening algorithm (figure 4). Physiotherapy will occur from Monday to Friday as there is no physiotherapy service available routinely at weekends.

The intervention group will receive an augmented programme with a target delivery of 90 min of active exercise per day, again from Monday to Friday. The physiotherapy sessions will consist of functional retraining (figure 3) and an individually tailored exercise programme, based on a muscle-strengthening algorithm (figure 4). The delivery of this treatment will be divided into one or more sessions depending on: the individual participant's tolerance of the programme; the need for other medical and nursing interventions; and the progression of the participant's recovery.

During the physiotherapy sessions, participants will be monitored closely, and if any of the following occur, the session will be stopped: MAP <60 mm Hg; heart rate <40 or >130 bpm; oxygen saturation <88% (or, if known respiratory disease, a 10% decrease from normal oxygen saturation); marked ventilator asynchrony; participant distress; new arrhythmias; myocardial ischaemia; concern for airway integrity; endotracheal tube removal; fall to knees; or any other significant event where the participant is unable to continue rehabilitation.

Apart from the difference in the intensity of physiotherapy, both groups will have the usual rehabilitation pathway in participating units.

Following discharge from Critical Care, both groups will receive the same, standard intensity of ward-based physiotherapy, and continue with their rehabilitation pathway. In line with NICE guidance, participants will receive an exercise diary to continue independently on discharge from hospital. Any patient readmitted to Critical Care will receive standard physiotherapy care during the second and any subsequent readmissions. All readmissions will be recorded.

### Outcomes

#### Primary outcome measure

The primary outcome measure is physical health as measured by the Short Form 36 Health Survey (SF-36) Physical Component Summary (PCS) score at 6 months after randomisation.

#### Secondary outcome measures

Mental health: the SF-36 Mental Component Summary (MCS) score.

Exercise capacity: the 6 min walk test.^13^

Muscle power: hand grip and quadriceps muscle strength using a dynamometer^14^ (see online supplementary appendix S1).

Physical functional ability: measured at Critical Care discharge using the Modified Rivermead Mobility Index.^15^

Activities of daily living (ADLs): ability to perform ADLs will be assessed using the Functional Independence Measure (FIM).^16^ The FIM and other questionnaires may be completed via a telephone call, rather than in person, at the 3-month and 6-month follow-up visits.

QoL: SF-36 and EQ-5D questionnaires will be administered to assess participants’ QoL. Utility values will be derived from the EQ-5D and from the SF-36 using the algorithm provided by the SF-6D.^17^ These will be used as the outcome measures in the economic analysis.

Outcome and location: survival status and place of residence will be recorded at hospital discharge, and 3 and 6 months following randomisation.

Delirium: before beginning rehabilitation, participants will be screened for delirium using the Confusion Assessment Method for the Intensive Care Unit.^18^

Ventilator-free days: defined as the number of days from randomisation (day 1) to day 28 on which a patient breathed without mechanical ventilation (includes non-invasive ventilation) if the period of unassisted breathing lasted at least 48 consecutive hours. Continuous positive airways pressure is considered to be unassisted breathing.

Health economic outcomes: utility scores will be generated using the SF-6D algorithm and the EQ-5D scores. Patient costs for hospital visits will be assessed at 6 months, using the Patient Costs Questionnaire (see online supplementary appendix S2).

The time schedule of assessments of participants is shown in table 1.

**Table 1 BMJOPEN2015008035TB1:** Schedule of data collection and outcome assessments

	Randomisation	Rehabilitation sessions	Critical Care discharge	Hospital discharge	3 Months from enrolment	6 Months from enrolment
Demographic and diagnostic data	X					
Severity of illness: APACHE II score	X					
Premorbid activity	X					
Sedation hold		X				
Safety screen		X				
Session duration		X				
Session milestones		X				
Adverse events		X				
Quality of life: SF-36 and EQ-5D				X	X	X
Six-minute walk test				X	X	X
Functional Independence Measure			X	X	X	X
Grip strength, both hands			X	X	X	X
Quad strength, both legs			X	X	X	X
Body mass index			X	X	X	X
Modified Rivermead Mobility Index			X			
Patient costs questionnaire						X

APACHE, Acute Physiology and Chronic Health Evaluation; SF-36, Short Form 36 Health Survey.

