### Sample size

The trial is powered to detect a difference of five points on our primary outcome (the PCS score of the SF-36 at 6 months following recruitment) between the intervention and control groups. In a previous study, we found that mean PCS at 6 months after hospital discharge was 34 with a SD of 10.^19^ This SD is similar to that reported at 6 months in 110 participants in the standard limb of the PRaCTICal UK 20 follow-up study (SD 11.7), and in a follow-up study of 252 critically ill patients in The Netherlands (SD 11.2).^21^ Taking a SD of 11, a five-point difference would give a medium effect size of 0.45. A sample size calculation based on a power of 80% to detect a five-point difference in SD at a significance level of 0.05 would require 77 participants in each group, a total of 154 for the trial. However, the 6-month mortality in this group of patients is known to be approximately 40%. In addition, we anticipate that we may lose a further 10% of participants to follow-up for other reasons. We will therefore need to recruit a total of 308 participants (154 in each group).

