## Analysis

### Statistical analysis

The PCS component of the SF-36 at 6 months following recruitment is the primary end point of the study. In order to test the primary hypothesis of no difference between the intervention and control groups, the principal analysis will examine the difference between the groups on this measure using Analysis of Covariance (ANCOVA) in order to adjust for the effects of covariates in the analysis. The normality of the outcome variable will be assessed and, if necessary, transformations considered although ANCOVA are robust to deviations from this distribution. The covariates to be considered will include stratification variables (unit, admission type and preadmission activity level) in addition to demographic variables such as age and gender. More basic illustrative analyses using the t test or non-parametric alternatives may also be undertaken while, in addition, summary statistics will be calculated.

A broadly similar approach will be used to analyse the secondary outcome measures (the MCS component of the SF-36, the 6 min walk test, FIM, grip strength, quadriceps strength and body mass index (BMI)) at both 3 and 6 months post-study entry, in addition to at hospital discharge. Additionally, the 3-month and hospital discharge data on the PCS component of the SF-36 will be analysed in this fashion, along with the FIM, grip strength and BMI outcomes at Critical Care discharge. Repeated measures methods (again based on analysis of variance) will be employed in order to examine these outcome measures longitudinally across collected time points. Standard survival data methods, such as Kaplan-Meier and the log rank test, will be used to compare survival between the groups at 3 and 6 months. We will also compare durations of Critical Care and hospital stay, in addition to the delirium and ventilator-free days measures.

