There are no planned interim analyses or stopping rules. An allowance for loss to follow-up has been included in the sample size calculation; data with missing observations due to loss to follow-up, as opposed to mortality, will be examined to determine both the extent of missing data and whether data are missing at random or are informative. If data are missing to a sufficient extent, the use of appropriate imputation techniques will be considered to allow for this in the analysis. All analyses will initially be performed on an intention-to-treat basis, although it may be useful to consider additional per-protocol analyses. We may base an analysis on groups defined by a dichotomisation (into long or short) length of stay in Critical Care, in addition to considering other subgroup analyses. A statistical analysis plan will be written and agreed by the Trial Oversight Committee (TOC) before analysis of the study data.

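### The ventilator-free days definition has no term for death, so unassisted days before a death by day 28 are credited and death is under-penalised

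*Protocol article*

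**What the plan says.** Under Secondary outcome measures the protocol article gives a full operational definition of ventilator-free days. The window is "defined as the number of days from randomisation (day 1) to day 28". The days that count are those "on which a patient breathed without mechanical ventilation (includes non-invasive ventilation) if the period of unassisted breathing lasted at least 48 consecutive hours". One further rule settles a borderline case: "Continuous positive airways pressure is considered to be unassisted breathing". Nothing is said about a patient who dies before day 28: the count is not set to 0 and survival to day 28 is not required.

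Under Statistical analysis the only statement on how the outcome is used is "We will also compare durations of Critical Care and hospital stay, in addition to the delirium and ventilator-free days measures". Survival has its own analysis: Kaplan-Meier and log rank methods "will be used to compare survival between the groups at 3 and 6 months". The missing-data text sets deaths apart ("data with missing observations due to loss to follow-up, as opposed to mortality, will be examined") and does not say how they enter other outcomes.

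Under Sample size the article states that "the 6-month mortality in this group of patients is known to be approximately 40"%. It gives no 28-day mortality and no time to liberation from ventilation.

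**The concern.** Ventilator-free days is meant to rank patients from worst to best over 28 days. Where mortality is high, that ranking makes sense only if death has a defined place in it. The written rule gives death no place of its own. Death stops the count, and the days already earned are kept. A patient weaned early who then dies can therefore tie with or outrank a survivor who was weaned late.

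What is at stake is how a secondary outcome is read. The abstract names it among the secondary outcomes, and the Introduction cites more ventilator-free days as a benefit in an earlier mobilisation trial, so a difference here would be taken as support for intensive physiotherapy. If the arms differ in both weaning and mortality, the written score can favour the arm with more deaths.

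**Working it through.** The documents give no figure for this outcome to reproduce. The check has three steps.

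**1. Example patients under the written definition** (days of liberation and death are illustrative; the day of death is not counted).

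| Patient | As written | Death by day 28 scored 0 |
|---|---|---|
| Off ventilator day 4, dies day 14 | 13 − 4 + 1 = 10 | 0 |
| Off day 19, survives | 28 − 19 + 1 = 10 | 10 |
| Off day 3, dies day 15 | 14 − 3 + 1 = 12 | 0 |
| Off day 20, survives | 28 − 20 + 1 = 9 | 9 |
| Never off, dies day 5 | 0 | 0 |

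The first two patients tie. The third, who dies, outranks the fourth, who survives.

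**2. Size of the gap between the two rules.** From the documents: 308 participants and about 40% dead by 6 months, so 0.40 × 308 ≈ 123 deaths, or about 62 per group. Assumed, because the documents do not give them: 28-day mortality p of 20 to 30%; time to liberation exponential with mean m = 9 days; death uniform over days 2 to 28 and independent of liberation.

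The rules differ only in patients who die, so gap = p × C, where C is the mean number of credited days among them. In continuous time, leaving out the 48 h condition,

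C = 15 − m + m² × (e^(−2/m) − e^(−28/m)) / 26.

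For m = 9, C = 8.36, so the gap is 0.20 × 8.36 = 1.7 days, 0.25 × 8.36 = 2.1 days and 0.30 × 8.36 = 2.5 days. Simulations with the 48 h condition give slightly less: 1.65, 2.08 and 2.48 in continuous time, and 1.5, 1.9 and 2.3 when counted in whole days. Hence roughly 1.5 to 2.5 days.

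Now drop independence. A patient who is never liberated and dies earns 0 under both rules. If 70% of deaths are of that kind and the rest behave as above, the gap is multiplied by 0.3 and becomes about 0.5, 0.6 and 0.75 days. At 90% it is about 0.17, 0.21 and 0.25 days.

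**3. Can the order of the arms change?** Let S be the mean score in survivors: S = 28 − m × (1 − e^(−28/m)), which is 19.40 for m = 9 and 20.24 for m = 8. C is 8.36 and 8.84 respectively.

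| | Arm A: m = 9, p = 20% | Arm B: m = 8, p = 25% |
|---|---|---|
| Death scored 0: (1 − p) × S | 0.80 × 19.40 = 15.5 | 0.75 × 20.24 = 15.2 |
| As written: add p × C | 15.5 + 1.7 = 17.2 | 15.2 + 2.2 = 17.4 |

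As written, B leads by 0.2 days. With deaths scored 0, A leads by 0.3 days. With the 48 h condition the written means are about 17.1 or 17.2 against 17.3 or 17.4, and the order is the same.

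This reversal also rests on independence. If 70% of deaths are in patients never liberated, the written means are 15.52 + 0.3 × 1.67 = 16.0 for A and 15.18 + 0.3 × 2.21 = 15.8 for B, and the two rules agree.

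**The case against.** A reader might infer that early death counts as a good outcome on this measure, or that extra deaths push it in the wrong direction. The definition does not support that. Days after death are not days on which the patient breathed, so death never adds to the score, and death while still ventilated with no earlier qualifying spell scores 0. Under the assumptions of step 2, with whole-day counting, the written mean falls as 28-day mortality rises through 20, 25 and 30%: 16.25, 15.72, 15.19. Scoring death as 0 gives 14.75, 13.85, 12.90. Mortality alone moves the written score the right way, but too little.

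A reader might also infer that length of stay is compared without regard to death, so that dying early passes for a short stay. The article says only that durations will be compared. It names no method and does not say whether a death is censored, excluded or counted as discharge. It also commits to a later plan: "A statistical analysis plan will be written and agreed by the Trial Oversight Committee (TOC) before analysis of the study data". Handling of death in a duration comparison is commonly left there, so this is not an error in the document. Nor does the Economic analysis section mention length of stay, so no distortion of costs can be read from it.

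Three further objections have weight. The gap in step 2 is a difference between two scoring rules, not a bias in the treatment effect; if weaning and mortality are equal in the arms, it cancels. Its size depends heavily on the assumed independence of death and weaning. And survival is compared separately, so a mortality difference would be visible beside this outcome.

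None of these removes the point. The article did not leave the outcome to the later plan: it fixes the window, the qualifying spell and the status of non-invasive ventilation and continuous positive airways pressure. A later plan would have to alter that rule, not just fill in a detail. A separate survival curve helps interpretation but leaves the scores unchanged.

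**Conclusion.** The point holds for ventilator-free days. The stated definition credits unassisted days before a death by day 28, and so lets a patient who dies tie with or outrank a survivor weaned late. That follows from the text alone.

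The numerical size is conditional. The excess over zero-for-death scoring is roughly 1.5 to 2.5 days per patient on average, given 28-day mortality of 20 to 30%, a mean of 9 days to liberation and death independent of weaning. It is well under 1 day if most deaths occur in patients never liberated. The reversal between arms is a demonstration that the order can change, with differences of only 0.2 to 0.3 days, and not a forecast for this trial. The matter is confined to a secondary outcome.

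**What to change.** Amend the definition so that any patient who dies by day 28 scores 0 ventilator-free days. Compare the arms with a rank-based test, since the score will have a cluster at 0, and report 28-day mortality by arm beside it.

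The cost is a sentence in the definition and one in the analysis plan, agreed before the data are analysed; the article says that the plan is still to be written and that the trial is in follow-up. No new data collection is evident: survival status is recorded, and the planned Kaplan-Meier analysis implies dates of death, though the article does not list the date as a data item, so this should be confirmed. The small downside is that the outcome becomes an explicit composite with mortality, and the report should say so.

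As a suggestion for the analysis plan only, Critical Care and hospital stay could be analysed as time to discharge alive with death as a competing event.
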